### Sample size

A 10% CR rate is assumed in patients diagnosed with hr-LARC, treated with chemoradiotherapy alone prior to surgery [30, 32]. Based on the available literature and a retrospective analysis of patients from our own institution a CR rate of 20% is hypothesised after neoadjuvant chemotherapy and chemoradiotherapy for hr-LARC [30, 32, 33]. A 5% significance level and a 90% power, resulted in a total of 121 required patients. A drop-out of 5% is expected, resulting in a total sample size of 128 patients.

### Recruitment

All eligible patients with hr-LARC presenting in one of the study centres will be identified by their physician and reviewed for eligibility during a MDT meeting.

### Data collection and management

Central data management will be performed by the research team of the Catharina Hospital Eindhoven. Local data management will be performed by the coordinating investigator or an in-hospital qualified local data management team. Data will be collected in a central study database with an electronic case report form (eCRF) according to the Good Clinical Practice guidelines and the Dutch legal requirements. Major protocol violations will be recorded.

### Statistical methods

Demographics, patient, and tumour characteristics will be presented for all patients. Continuous data will be reported as mean with a standard deviation or as median with an interquartile range or 95% confidence interval, depending on the distribution. Categorical data will be reported as count, including a percentage. All statistical tests will be two-sided and a P-value of less than 0.05 will be considered as statistically significant.

The proportion of patients with a CR, defined as a pCR or a sustained cCR, will be compared to the CR rate of a comparable group of patients treated with chemoradiotherapy alone before surgery, as described in the available literature (i.e. 10%), performing a chi-squared goodness-of-fit-test.

The Kaplan–Meier method will be used to display survival curves. In addition, Hazard Ratio’s will be calculated using the Cox proportional hazard regression model and will be accompanied by 95% confidence intervals. Perioperative morbidity, surgical characteristics, and histopathological findings will be presented for all patients treated with a surgical resection. The incidence of toxicity related to neoadjuvant treatment will be presented separately for neoadjuvant chemotherapy and chemoradiotherapy. Health-related quality of life is graphically presented across all time points. Moreover, quality of life will be compared during those different time points using the ‘repeated measures ANOVA’. Incremental costs are calculated for the extra costs per additional patient alive and the extra costs per additional quality adjusted life year, respectively. The 95% confidence intervals for (differences in) costs and health outcomes will be generated by non-parametric bootstrapping, drawing samples of the same size as the original samples.

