#### Questionnaires

All patients participating in the study will receive validated quality of life questionnaires after informed consent. Patients will be asked to complete the EORTC QLQ-C30, QLQ-CR29 (from the European Organisation for Research and Treatment of Cancer Quality of Life Group), and EQ-5D-5L (from the EuroQoL Group, Rotterdam, the Netherlands) at inclusion, 3, and 12 months post-operatively [61–63]. Patients receive questionnaires either by email or on paper, according to their own preferences.

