### Outcomes

The primary outcome of this study is the CR rate, defined as the presence of a pCR or a cCR. A pCR is defined as the absence of viable tumour cells at pathological examination of the resected specimen [22, 64]. A cCR is defined as the sustained absence of tumour tissue 1 year after treatment as assessed during clinical evaluations [16, 17]. Since the MEND-IT study is a phase II study, the CR rate observed in this trial will be compared to the CR rate as described in current literature for patients with hr-LARC treated with chemoradiotherapy alone (i.e. 10%) [32, 33]. In addition, the results of the MEND-IT trial will be compared to results of comparable cohorts treated with different treatment regimens.

Secondary objectives comprise the number of patients proceeding to surgery, the 3- and 5-year local recurrence-free, distant metastasis-free, progression-free, disease-free and overall survival. In addition, radiological response, pathological response, R0 resection rate, toxicity, treatment compliance rate, surgical morbidity, quality of life, and costs will be evaluated. Local recurrence-free survival is defined as the interval between surgery and a local recurrence. Metastasis-free survival is defined as the interval between inclusion and the detection of distant metastases. Progression-free survival will be calculated from inclusion onwards to the date of clinically or histopathologically proven distant metastases, a local recurrence, or the date of death from any cause, whichever occurs first. Disease-free survival will be calculated from the date of surgery onwards or the date of the second restaging MRI in case of a cCR until the date of a local recurrence, distant metastasis, or death from any cause, whichever occurs first. Overall survival will be calculated from the date of inclusion until the date of death from any cause. Toxicity from neoadjuvant treatment will be presented according to the NCI (US National Cancer Institute) Common Terminology Criteria for Adverse Events (CTCAE) v5.0 [65]. Perioperative complications will be presented according to the Clavien-Dindo grading system [66]. Pathological response will be presented according to the Mandard grading system [64].

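### Repeated measures ANOVA for quality of life in its classical form uses only patients with all three questionnaires; a mixed model would keep every form collected

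*Protocol article*

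**What the plan says.** Quality of life is one of several secondary outcomes (protocol article, Outcomes: "toxicity, treatment compliance rate, surgical morbidity, quality of life, and costs will be evaluated"). Under Questionnaires, "All patients participating in the study will receive validated quality of life questionnaires after informed consent". The instruments are the EORTC QLQ-C30, the QLQ-CR29 and the EQ-5D-5L, completed "at inclusion, 3, and 12 months post-operatively".

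Statistical methods plans a graphical display over all time points and adds that "quality of life will be compared during those different time points using the ‘repeated measures ANOVA". The general rule for tests is: "All statistical tests will be two-sided and a P-value of less than 0.05 will be considered as statistically significant". The article does not say how patients with an incomplete series of questionnaires enter the ANOVA.

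**The concern.** Classical repeated measures ANOVA needs a value at every time point for each patient. One missing form then removes that patient's other forms too, including a baseline form that was completed.

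The design makes incomplete series likely:

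- Under Neoadjuvant chemotherapy and Treatment evaluation, patients found to have unresectable or metastatic disease move to palliative treatment. They have no operation from which a post-operative form could be timed.
- Watch-and-wait patients also have no operation. For disease-free survival the Outcomes section gives complete responders another starting date, the second restaging MRI. Questionnaires names no such date for the forms.
- The population is selected for poor prognosis, so progression and death before the 12-month form are to be expected.

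Three things are at stake: questionnaires that patients took the trouble to complete, the precision of the comparison between time points, and the question of which patients the result describes.

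**Working it through.** **The plan's own figure.** The article gives no figure for quality of life. Its one sample-size calculation concerns the primary endpoint: "A 10% CR rate is assumed in patients diagnosed with hr-LARC", against a hypothesised 20%; "A 5% significance level and a 90% power, resulted in a total of 121 required patients". For a one-sample proportion with two-sided 5% significance:

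n = [(1.960 × √(0.1 × 0.9) + 1.2816 × √(0.2 × 0.8)) / 0.1]² = [(0.588 + 0.5126) / 0.1]² ≈ 121.1

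Allowing for 5% drop-out, 121 / 0.95 = 127.4, which rounds up to 128. Both stated figures reproduce, and nothing below changes them.

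**Patients left in the ANOVA.** Inputs: N = 128 (Sample size); complete baseline forms (assumption); completion c at each of the two follow-ups (assumption, shown as a range). If missingness is independent between the two forms, N × c² patients remain. If it is fully nested, so that the same patients miss both forms, N × c remain.

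| c | Independent: 128 × c² | Nested: 128 × c |
|---|---|---|
| 0.95 | 115.5, about 116 | 121.6, about 122 |
| 0.90 | 103.7, about 104 | 115.2, about 115 |
| 0.80 | 81.9, about 82 | 102.4, about 102 |
| 0.70 | 62.7, about 63 | 89.6, about 90 |

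**Questionnaires discarded.** Forms collected are 128 × (1 + 2c). Forms used are 3 × 128 × c² if independent and 3 × 128 × c if nested.

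- Independent: 1 − 3c² / (1 + 2c) gives 13%, 26% and 39% at c = 0.9, 0.8 and 0.7.
- Nested: 1 − 3c / (1 + 2c) gives 7.7% at c = 0.8 (0.2 / 2.6) and 12.5% at c = 0.7 (0.3 / 2.4).

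**Standard errors of visit means, complete cases against all available forms.**

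- Independent, follow-up visits: √(0.8 / 0.64) = 1.12 and √(0.7 / 0.49) = 1.20.
- Independent, baseline: √(1 / 0.64) = 1.25 and √(1 / 0.49) = 1.43.
- Nested: no loss at the follow-up visits. At baseline √(1 / 0.8) = 1.12 and √(1 / 0.7) = 1.20.

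**Change from baseline, by simulation.** All inputs are assumptions: 128 patients, SD 20, true means 70, 62 and 66 on a scale where higher is better, within-patient correlation 0.4 or 0.6, 500 runs per scenario. Complete-case estimates were compared with a maximum-likelihood fit of an unstructured normal model, which is what a mixed model for repeated measures delivers.

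- Forms missing completely at random, correlation 0.6: the standard error of the 12-month change was 1.80, 1.97 and 2.28 for complete cases at 10%, 20% and 30% missing per form, against 1.69, 1.67 and 1.91 for the likelihood fit.
- Forms more often missing after a worse earlier score: complete-case means were too high by about 3 to 8 points at baseline and at 3 months, and by about 2 to 6 points at 12 months. The 3-month change was almost unbiased. The 12-month change was biased downward by about 1 to 3 points. The likelihood fit stayed within about 0.2 points throughout.

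**The case against.** The strongest reply is that complete-case deletion is inferred. The article is condensed, and the handling of missing forms may be set out in a full protocol or analysis plan that is not shown. This stands in part: the article nowhere says that incomplete patients are dropped, and its silence on missing data is not the point. But it does name the method, and in its classical form that method analyses complete series only. A better-suited method can be named in the same place.

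Secondly, the completion rates are assumed. The only attrition figure for this trial is the 5% drop-out in Sample size, and it was not set for questionnaires. At 5% missing per form the loss is small: 116 to 122 of 128 remain. Independence is also the less favourable of the two patterns shown. Progression and death tend to remove both forms from the same patient, which moves the result towards the nested column. The figures of 82 and 63 should therefore not be read as expected numbers.

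Thirdly, a reader might infer that the change from baseline will look too favourable because the healthiest patients remain. The documents do not support that direction. The plan compares time points, so errors in the visit means partly cancel. In the simulation the 12-month change erred downward, because selection on good earlier scores brings regression to the mean. Leaving out watch-and-wait patients, who are responders, could also shift the means the other way.

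A reader might also infer a breach of sphericity from unequal gaps. The treatment timeline puts the 3-month form about 41 to 53 weeks after inclusion: 0–4 weeks to start, 10 to the sixth cycle, 3–6 to chemoradiotherapy, 5–5.6 of chemoradiotherapy, 10–14 to surgery, then 13. The next gap is 9 months, about 39 weeks. The gaps may be nearly equal, spacing alone does not settle sphericity, and standard corrections exist. The point does not need this argument.

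**Conclusion.** The point holds in limited form. In its classical form the named method discards questionnaires already collected, loses precision once any follow-up form is missing, and restricts the comparison to a selected subset. Mean scores in that subset are probably too high if sicker patients drop out. The sign of any bias in the change from baseline is uncertain.

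The size depends on assumed completion and on how missing forms cluster. It runs from a handful of patients lost at 95% completion to about half at 70% with independent missingness. The loss of precision follows from the method; the selection effect depends on why forms are missing. Because this is a within-arm comparison of a secondary outcome, with the primary endpoint and sample size untouched, severity is low to moderate.

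**What to change.** In Statistical methods, replace the ANOVA with a linear mixed model for repeated measures for each quality-of-life score: time as a categorical factor, unstructured covariance, all available observations included. Report the number of forms expected and received at each time point.

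State the limits alongside. The model is valid under missing at random. It does not cure missingness that depends on unobserved scores, or truncation by death, and it does not settle when a patient without surgery completes a form timed from surgery.

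The cost is a sentence or two before the data are analysed. The data are the same and standard software suffices.

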### Data monitoring

A data safety monitoring board (DSMB) has been appointed to monitor patients’ safety and to advice the study steering committee on the continuation of the study after the interim analysis. The interim analysis will be performed when 50 patients have undergone surgery or entered a W&W approach. The number of patients not able to complete chemoradiotherapy and the number of patients with major postoperative morbidity (i.e. Clavien-Dindo ≥ 3) will be analysed [66]. Results will be discussed during a meeting of the DSMB, subsequently resulting in a recommendation about the continuation of the study. A premature termination of the study may be advised if more than 35% of the patients is unable to complete chemoradiotherapy due to treatment-related toxicity, or if more than 50% of the patients experience severe postoperative complications (i.e. Clavien-Dindo ≥ 3).

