## Discussion

Despite encouraging results of neoadjuvant chemotherapy in patients diagnosed with LARC, the clinical applicability remains a topic of debate due to varying inclusion criteria, varying treatment strategies, and the lack of improvement in overall survival in previous studies [31]. The addition of (intensified) neoadjuvant chemotherapy to the current treatment regimen may improve surgical and oncological outcomes in some patients, but may also prove unfeasible in many patients and even induce unnecessary risks [32, 33]. This highlights the need for uniform guidelines regarding patient selection and treatment regimens in LARC [26, 27, 31]. The aim of this multicentre, single-arm phase II study is to evaluate the CR rate of intensified neoadjuvant treatment, consisting of triplet chemotherapy (FOLFOXIRI) prior to chemoradiotherapy, in a select, homogeneous group of rectal cancer patients meeting the MEND criteria, and who are therefore facing the worst prognosis. We refer to this subgroup of locally advanced rectal cancer as “hr-LARC”. 

Triplet chemotherapy has been shown to be feasible and effective in patients with rectal cancer [32, 56]. Moreover, an improved tumour response has been described with FOLFOXIRI (triplet) chemotherapy compared to doublet chemotherapy in metastatic colorectal cancer [56–58]. The PRODIGE 23 trial observed an enhanced CR rate and 3-year DFS for patients treated with neoadjuvant triplet chemotherapy, consisting of FOLFIRINOX, prior to standard treatment with chemoradiotherapy and surgery [32]. Despite the intensity of triplet chemotherapy with the occurrence of serious adverse events in 20% of the patients, the vast majority of the patients in the experimental arm was able to proceed to chemoradiotherapy (95%) and surgery (92%) afterwards [32]. Nevertheless, patients with LARC facing the worst prognosis were underrepresented. We hypothesised that patients with hr-LARC, meeting the MEND criteria, may benefit most from intensive treatment in an early stage of the disease. Hence, the addition of triplet chemotherapy consisting of FOLFOXIRI to current standard treatment has been suggested.

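### The interim safety measures and both advisory limits register FOLFOXIRI toxicity only indirectly, through chemoradiotherapy non-completion or postoperative morbidity

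*Protocol article*

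**What the plan says.** **Interim content** (Protocol article, Data monitoring). One interim analysis takes place once 50 patients have had surgery or entered watch and wait. It covers "The number of patients not able to complete chemoradiotherapy and the number of patients with major postoperative morbidity", the latter meaning Clavien-Dindo grade 3 or higher.

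**Limits** (same section). The DSMB may advise stopping if "more than 35% of the patients is unable to complete chemoradiotherapy due to treatment-related toxicity", or if more than half have severe postoperative complications. The limits are advisory. The DSMB also has a general remit to watch over patient safety.

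**What is experimental** (Aim, design, and study setting; Neoadjuvant chemotherapy; Chemoradiotherapy; Surgery). The trial adds six cycles of FOLFOXIRI. Chemoradiotherapy and surgery follow standard of care.

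**Toxicity data** (Outcomes; Statistical methods). CTCAE v5.0 toxicity and treatment compliance are secondary outcomes, and "The incidence of toxicity related to neoadjuvant treatment will be presented separately for neoadjuvant chemotherapy and chemoradiotherapy". Neither is linked to the interim analysis.

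**Serious adverse events** (Harms). Reports go to the coordinating investigator within 24 hours and from there to the ethics committee. No route to the DSMB is stated.

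**The concern.** Both interim quantities are observed after FOLFOXIRI has ended. Between FOLFOXIRI and those observations the plan allows dose reductions at the oncologist's discretion and an interval of 3 to 6 weeks before chemoradiotherapy. The Discussion defends the sequence partly because it gives patients time to regain fitness before surgery. Toxicity can therefore be severe, end FOLFOXIRI early, and resolve before anything is counted.

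The Discussion itself warns that intensified treatment could prove unfeasible for many patients and carry needless risk. The two named quantities do not describe FOLFOXIRI feasibility directly. At stake is the evidence behind the DSMB's advice on continuing: the named counts could look reassuring while the added regimen is poorly tolerated.

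**Working it through.** **1. Trace one patient through the two counts.** Severe toxicity after cycle 2; FOLFOXIRI stopped for good; chemoradiotherapy completed; uneventful operation or watch and wait. Chemoradiotherapy non-completion: 0. Clavien-Dindo 3 or higher: 0. This holds whatever denominator is used.

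**2. The article's own figures for the cited triplet trial.** The Discussion reports "Despite the intensity of triplet chemotherapy with the occurrence of serious adverse events in 20% of the patients", while 95% went on to chemoradiotherapy and 92% to surgery. Assume these events occurred before chemoradiotherapy. At most 100% − 95% = 5% of patients could have had an event and not reached chemoradiotherapy. So at least 20% − 5% = 15% had one and still went on, which is at least 15/20 = 75% of those affected. These patients could enter the first count only by later failing to complete chemoradiotherapy.

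**3. What the 35% limit responds to.** The article gives no operating characteristics for either limit, so there is no stated figure to reproduce. With an assumed denominator of 50, more than 35% means more than 17.5, that is 18 or more. For a true non-completion rate p, the crossing probability is P(X ≥ 18), X ~ Binomial(50, p):

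| p | 5% | 15% | 20% | 25% | 30% | 35% | 40% |
|---|---|---|---|---|---|---|---|
| P(X ≥ 18) | 1.5e-11 | 0.0002 | 0.006 | 0.055 | 0.22 | 0.49 | 0.76 |

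On their own these values show only that a 35% limit is rarely crossed when the true rate is low, as it should be. The question is how p relates to FOLFOXIRI toxicity. Let g be the share with severe FOLFOXIRI toxicity and s the share of those who therefore fail chemoradiotherapy. With other causes of failure set to zero, p = g × s. With g fixed at 50%:

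| s | p = 0.50 × s | P(X ≥ 18) |
|---|---|---|
| 10% | 5% | 1.5e-11 |
| 25% | 12.5% | 0.00002 |
| 50% | 25% | 0.055 |
| 100% | 50% | 0.98 |

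The amount of severe toxicity is the same in every row. The limit sees only the part that stops chemoradiotherapy. Both g and s are assumptions; the article gives neither for this population.

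**4. Toxicity that does stop chemoradiotherapy.** Let f be the share kept from chemoradiotherapy by FOLFOXIRI toxicity and c = 10% (assumed) the non-completion rate among those who start it. If the f patients count, p = f + (1 − f) × c:

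| f | p | P(X ≥ 18) |
|---|---|---|
| 10% | 0.10 + 0.90 × 0.10 = 0.19 | 0.004 |
| 20% | 0.20 + 0.80 × 0.10 = 0.28 | 0.14 |
| 30% | 0.30 + 0.70 × 0.10 = 0.37 | 0.61 |
| 40% | 0.40 + 0.60 × 0.10 = 0.46 | 0.94 |

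If they do not count, p stays at 10% and the probability is 7.6e-7 for every f. The section does not say which applies. The trigger is defined by patients who reached surgery or watch and wait, and the denominator of the limit is not stated.

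**5. The second limit.** More than 50% of 50 is 26 or more. The crossing probability is 0.001, 0.057, 0.44 and 0.90 at true complication rates of 30%, 40%, 50% and 60%. FOLFOXIRI contributes here only through carry-over into surgery.

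**The case against.** A reader might infer that FOLFOXIRI toxicity can never count towards stopping. The article does not support that. The first limit speaks of treatment-related toxicity without confining it to chemoradiotherapy, and FOLFOXIRI comes first. A patient too unwell from FOLFOXIRI to start or finish chemoradiotherapy can be read as counting, and step 4 shows the limit can then respond strongly. Carry-over could also raise surgical morbidity and reach the second limit.

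Nor is the interim analysis shown to be the only safeguard. The DSMB's remit is general, the limits are advisory and not said to be exhaustive, and serious adverse events are reported within 24 hours. Nothing bars the DSMB from acting on FOLFOXIRI toxicity.

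The chosen measures also have a rationale: the Background and Discussion ask whether patients given induction chemotherapy still reach chemoradiotherapy and surgery. A shortened FOLFOXIRI course is not in itself a failure of the strategy. The cited triplet trial is presented as evidence of feasibility, not as a missed safety signal. Finally, this is a condensed article, and the full protocol or a DSMB charter, not shown, may list more.

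All of this stands, and it limits the point. It does not remove it. The article does state what the interim analysis contains, and a general remit does not put FOLFOXIRI data into that analysis. The described reporting route for serious adverse events does not name the DSMB. Early discontinuation or non-serious grade 3 toxicity need not be a serious adverse event at all.

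**Conclusion.** The point holds in limited form. The two interim quantities and both advisory limits capture FOLFOXIRI toxicity only where it prevents completion of chemoradiotherapy or shows up as major postoperative morbidity. Severe toxicity or early discontinuation that does neither enters no count, at any frequency.

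The size depends on the share of severe toxicity that goes on to stop chemoradiotherapy, which the article does not give. With 50% severe toxicity, the chance of crossing the 35% limit runs from about 1.5e-11 to 0.98 as that share goes from 10% to 100%. This assumes a denominator of 50, independent patients and no other cause of non-completion.

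This is a worthwhile, inexpensive improvement to a stated analysis. It is not an internal contradiction, and it does not show that the trial's safety oversight as a whole is blind to the study regimen. It leaves the primary analysis and sample size untouched.

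**What to change.** In Data monitoring, and in the DSMB charter if there is one, add to the quantities analysed at the interim, for all patients who started FOLFOXIRI by the data cut:

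- the number who stopped FOLFOXIRI early because of toxicity;
- the number with CTCAE v5.0 grade 3 or higher toxicity in the FOLFOXIRI phase;
- the number of treatment-related deaths.

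State that the DSMB's recommendation also takes these into account. Whether any of them carries a limit, and what it would be, is for the steering committee and DSMB; none is proposed here.

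The cost is a sentence and one extra table, drawn from toxicity and compliance data that the plan already collects. The downside is a slightly higher chance of a discussion about stopping.
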